## Abstract

**Background:**

Transfusion-transmitted infections (TTIs) are a global health challenge. One new approach to reduce TTIs is the use of pathogen reduction technology (PRT). In vitro, Mirasol PRT reduces the infectious load in whole blood (WB) by at least 99%. However, there are limited in vivo data on the safety and efficacy of Mirasol PRT. The objective of the Mirasol Evaluation of Reduction in Infections Trial (MERIT) is to investigate whether Mirasol PRT of WB can prevent seven targeted TTIs (malaria, bacteria, human immunodeficiency virus, hepatitis B virus, hepatitis C virus, hepatitis E virus, and human herpesvirus 8).

**Methods:**

MERIT is a randomized, double-blinded, controlled clinical trial. Recruitment started in November 2019 and is expected to end in 2024. Consenting participants who require transfusion as medically indicated at three hospitals in Kampala, Uganda, will be randomized to receive either Mirasol-treated WB (*n* = 1000) or standard WB (*n* = 1000). TTI testing will be performed on donor units and recipients (pre-transfusion and day 2, day 7, week 4, and week 10 after transfusion). The primary endpoint is the cumulative incidence of one or more targeted TTIs from the Mirasol-treated WB vs. standard WB in a previously negative recipient for the specific TTI that is also detected in the donor unit. Log-binomial regression models will be used to estimate the relative risk reduction of a TTI by 10 weeks associated with Mirasol PRT. The clinical effectiveness of Mirasol WB compared to standard WB products in recipients will also be evaluated.

**Discussion:**

Screening infrastructure for TTIs in low-resource settings has gaps, even for major TTIs. PRT presents a fast, potentially cost-effective, and easy-to-use technology to improve blood safety. MERIT is the largest clinical trial designed to evaluate the use of Mirasol PRT for WB. In addition, this trial will provide data on TTIs in Uganda.

**Trial registration:**

Mirasol Evaluation of Reduction in Infections Trial (MERIT) NCT03737669. Registered on 9 November 2018

## Introduction

Transfusion-transmitted infections (TTIs) of known and unknown pathogens are a global health challenge [1]. The United Nations Programme on HIV and AIDS (UNAIDS) has suggested up to 1% of new HIV infections per year may be attributable to transfusions [2]. A wide variety of organisms, including bacteria, viruses, prions, and parasites, can be transmitted through whole blood or blood product transfusions [3].

In low-income countries, TTIs are extremely common. Yet targeted screening for pathogens is limited in scope, serving only to address risk from a few, highly selected known pathogens. For example, the Ugandan Blood Transfusion Service (UBTS), similar to most other blood collection centers throughout sub-Saharan African, only screens blood for human immunodeficiency virus (HIV), hepatitis B virus (HBV), hepatitis C virus (HCV), and syphilis. Despite screening, retrospective testing has detected these viruses in screened blood due to inadequate methods and acute infections prior to marker positivity in blood [4]. Additional known viruses that may be transmitted by transfusion include human T-lymphotropic virus types I and II (HTLV-I and HTLV-II), hepatitis E virus (HEV), and arboviruses including West Nile virus, Zika virus, dengue virus, and human herpesvirus 8 (HHV-8) [5–11]. Furthermore, blood for transfusion throughout sub-Saharan Africa (SSA) is not screened for bacteria or parasites, despite regionally endemic infections that are known to be transfusion transmissible (e.g., malaria) [12]. Transfusion recipients remain susceptible to untested or unknown infectious agents. These limitations are amplified in regions of the world where blood safety testing may not be closely monitored or due to disruptions in laboratory supply chains such as during disease outbreaks (e.g., Ebola) or civil strife.

One innovative approach to reduce the threat posed by TTIs is the use of pathogen reduction technology (PRT). This technology has been approved by the European Medicines Agency (EMA), and a Conformitè Europëenne (CE) Mark was obtained for Mirasol-treated WB in 2015. In brief, Mirasol PRT, developed by Terumo BCT, requires riboflavin to be mixed into a whole blood (WB) unit, which is then exposed to UV light (313 nm) for 1 h [13]. The chemical reaction between riboflavin and UV light prevents DNA and RNA replication. Disruption of nucleic acids occurs through two independent mechanisms: (1) UV light breaking bonds in nucleic acids and (2) photo-activation of riboflavin molecules interacting with nucleic acids, leading to electron transfer and irreversible modifications to specific functional groups of nucleic acids (e.g., guanine) [14–16]. Agents with nucleic acids, including viruses, parasites, and bacteria, or white blood cells, are inactivated or destroyed by varying degrees. In vitro, Mirasol PRT reduces the infectious load in treated WB for most pathogens by 99.9% [14–18]. Data have demonstrated Mirasol reduces parasites (*Trypanosoma cruzi* [19], *Babesia microti* [20], *Babesia divergens, Leishmania donovani* [21], and *Plasmodium falciparum* [22]), bacteria (*Yersinia enterocolitica*, *Acinetobacter baumannii*, and *Serratia liquefaciens* [17, 23]), and viruses (HIV, HBV, and HCV [17, 18, 24, 25]) by three to seven logs. Destruction of WBCs reduces the risk of transfusion-associated graft-versus-host disease (TAGvHD) and is comparable to using gamma irradiation [26]. Cells without nucleic acids, i.e., RBCs and platelets, suffer only minor cellular damage while plasma proteins are well preserved [27, 28].

A single-center randomized trial of 226 participants in Ghana evaluated if Mirasol-treated WB reduces transfusion-transmitted malaria (TTM) [29]. The incidence of TTM was significantly lower in the Mirasol-treated WB group (1/28 [4%] compared to standard group 8/37 [22%]; *p* = 0.039). This small trial did not assess other TTIs or adverse outcomes that can only be evaluated with larger and longer trials. The objective of the Mirasol Evaluation of Reduction in Infections Trial (MERIT) is to investigate whether Mirasol PRT can prevent TTM as well as six other TTIs, namely HIV, HBV, HCV, HEV, HHV-8, and bacteria in vivo.

MERIT trial is a prospective, randomized, double-blind, controlled superiority clinical trial among individuals requiring WB transfusions in Uganda.

## Methods/design

Recruitment started in November 2019 and is expected to run until 2024. Two thousand patients will be enrolled and randomized (1:1) to receive either Mirasol-treated or standard-issue WB transfusions and followed up for 10 weeks. The clinical trial registration number is NCT03737669.

### Blood supply

The UBTS is the National Blood Service responsible for all blood transfusion and safety activities for the entire country. It is a semi-autonomous and centrally coordinated organization within the Ugandan Ministry of Health. It has a network of eight regional blood banks and six blood collection centers whose activities include donation, storage processing of blood, and distribution of processed blood to all health facilities whether government or private countrywide. Blood is distributed by UBTS to 277 health care facilities all over the country. In 2012, the UBTS collected 203,390 units of blood nationally. All blood donors (100%) are anonymous volunteers; there are no paid donors. UBTS tests all blood in a quality-controlled manner for HIV antigen-antibody, HBV surface antigen, HCV antibodies, and syphilis by rapid plasma reagin (RPR). TTI testing is done on blood that is drawn into the sample diversion pouch. Standard blood units/components supplied by UBTS are not leukoreduced nor are they gamma irradiated. In the standard arm of the trial, participants receive WB from regular collections that has undergone routine testing but has not been modified in any way. Intervention arm participants receive blood that in addition to the routine testing has been treated with Mirasol PRT illumination within 8 h of collection.

### Participants

The trial is being conducted by Makerere University-Johns Hopkins University Research Collaboration (MU-JHU) in Kampala, Uganda. The enrolment sites include the Mulago National Referral Hospital (MNRH), Kawempe Specialized National Referral Hospital (KSNRH), and Uganda Cancer Institute Mulago Specialised Women and Neonatal Hospital (UCI). The MNRH, located in Kampala, is the largest public referral and teaching hospital in Uganda with 1500 beds and approximately 3000 patients at any one time and includes the Orthopaedics Department, Surgery Department, and Casualty (i.e., Emergency) Unit. KSNRH is a public 170-bed hospital in Kampala that provides specialist obstetric, gynaecologic, and neonatal care. The UCI is the primary provider of specialized cancer treatment throughout Uganda.

Patients at these locations are eligible for the study if they meet the following inclusion criteria: (1) willing to participate in the study and the patient or legally authorized representative has given written informed consent; (2) transfusion necessary based on a hemoglobin of less than 7 g/dL or clinical judgment of attending physician following the national guidelines; (3) patient agrees to return to the hospital for follow-up visits; and (4) the doctor judges that the patient will be able to complete follow-up visits over the next 10 weeks.

Exclusion criteria (either permanent or temporary) are as follows: (1) presence of red cell alloantibodies; (2) incompatible red cell cross-match (at enrollment prior to first transfusion); (3) expected to require plasma or platelets within the next 10 weeks outside of the WB provided in the trial; (4) blood group Rhesus negative; (5) blood type AB (due to concern of limited supply); (6) weight < 30 kg (due to concern for sufficient blood draws to detect bacteria and other TTIs); (7) HIV-infected; (8) clinical suspicion of sepsis; (9) anti-malarial treatment or indication to be receiving malaria prophylaxis (e.g., sickle cell disease or ongoing pregnancy) within 7 days prior to randomization; (10) fever (central body temperature greater than 38.5 °C); (11) transfusion(s) of a blood product within 1 month prior to randomization; (12) acute or chronic medical disorder that, in the opinion of the investigator, would impair the ability of the patient to receive protocol treatment; and (13) previously enrolled and randomized in this trial or any other pathogen reduction trial.

### Randomization

Patients for whom a transfusion has been prescribed are referred to the study team by the attending physician or nurse. Participants who meet the eligibility criteria are assigned in a 1:1 ratio to either the control or treatment group using permuted block randomization. Participants may only be enrolled and randomized once. Randomization occurs only after confirming both Mirasol and control WB are available. The start of study treatment is defined as the initiation of the first WB transfusion. Participants receive all transfusions in the designated arm for up to 10 weeks after randomization.

### Blinding

Study personnel administering the transfusions and monitoring the participants for safety are blinded to the randomized treatment assignment. The study blood transfusion service laboratory technologists open the serial envelopes that have pre-assigned randomization to the study arm and study ID number. The technologists are responsible for assigning the participants the randomization and also for issuing the study blood. Mirasol-treated and standard WB differ slightly in the confirguation of the blood bag. Blinding of study staff and participants is maintained by use of blood bag cover. If it becomes necessary to unblind a specific participant’s assignment, e.g., for emergency medical management, the principal investigator will contact the technologists and obtain the treatment assignment of the subject. The Data and Safety Monitoring Board (DSMB) will be notified of the event within 2 business days.

### Assignment of intervention

The UBTS has a quality control program and follows the WHO recommended criteria for WB collection of 450 mL±10% with a hematocrit of 35–50% [30]. We are following all currently CE-marked, approved labeling criteria for standard WB or Mirasol-treated WB. Mirasol-treated units have an expiry date of 21 days assuming they are illuminated for PRT within 8 h of collection. For the trial, we also use standard units only up to 21 days and if not used, the units are returned to UBTS for re-issue as the expiry date for standard units is 35 days. Blood is stored at 1–6^o^C.

The decision to transfuse is made by the attending physician. Indications are specific to the individual patients and thus may vary by underlying pathology. The attending physician then refers the patient to the study. A study nurse/counselor gives the patient information about the study and obtains informed consent to join the study, and additional consent for sample storage and genetic testing is also sought. The participant is then screened for the study by a study doctor and samples drawn for testing. If found eligible, they are randomized and enrolled into the study.

Transfusion recipients are followed up for 10 weeks and evaluated six times, five of which include the collection of blood samples (Figs. 1 and 2). The parentheses give window periods for sample draws:
*Pre-transfusion*: enrollment of the recipient and blood collected to evaluate baseline infectious status and RBC compatibility and antibody identification. RBC compatibility and antibody identification consist of verifying the ABO group of the unit, ABO/Rh testing and 37oC Coombs antibody screen for the recipient, and a serological cross-match at room temperature; in the event that a participant develops a clinically significant RBC alloantibody during the study and requires further transfusion, appropriate 37°C pre-transfusion testing/cross-match will be performed.*At 2–6 h following transfusion*: assess hemoglobin increment with CBC and clinical evaluation for possible acute transfusion reactions, as defined by the US CDC Hemovigilance criteria [31].*Within 48 h (+ 1 day)* of each transfusion: blood collected for bacterial culture and malaria identification.*At 7 days (− 1 to + 2 days)* after the transfusion: obtain brief medical history focused on signs or symptoms of transfusion reactions and infections with HIV, HBV, HCV, HEV, HHV-8, or malaria. Blood collected for TTI testing and evaluation for transfusion reaction.*At 4 weeks (−4 to + 7 days)* after the transfusion: obtain brief medical history focused on signs or symptoms of infection with HIV, HBV, HCV, HEV, HHV-8, or malaria. Blood collected for TTI testing.*At 10 weeks (−7 to + 14 days)* after the first transfusion: obtain brief medical history focused on signs or symptoms of transfusion reactions and infections with HIV, HBV, HCV, HEV, HHV-8, or bacteria. Blood collected for TTI testing and evaluated for delayed transfusion reaction/new antibodies with antibody screen.

**Fig. 1 Fig1:**
[figure not shown]
Schedule of enrolment, intervention, and assessments

**Fig. 2 Fig2:**
[figure not shown]
Donor blood and recipient evaluation

Individuals who require additional transfusions are followed as above as long as they receive the additional transfusions within the first 6 weeks of their initial transfusion (i.e., they will be evaluated at 48 h, day 7, and day 28 of both the first and any subsequent transfusions). The visits are combined if they fall within the same window. However, once the individual reaches week 10 from the initial enrollment and transfusion, their follow-up ends. If individuals require transfusion support for transfusions received after the first 6 weeks of study participation, they still receive study blood transfusions as per their randomization until study exit at 10 weeks but do not have additional follow-up visits. To encourage adherence to study procedures, participants are compensated for their time and transportation for each scheduled visit. Participants are also eligible to withdraw from the trial at any stage.

In case of a transfusion reaction, the transfusion is stopped and the patient evaluated. After the relevant checks and investigations have been done, the transfusion may or may not be restarted. The participant’s trial arm is maintained for all future transfusions. Participating in the trial should not affect the usual patient care or require any alteration to concomitant medication.

### Intervention outcomes

The primary endpoint of this study is the incidence of any pre-defined viral, bacterial, or parasitic TTI: HIV, HBV, HCV, HEV, HHV-8, bacteria, or malaria in a previously negative recipient for the specific TTI as indicated by changes in laboratory findings at day 2, day 7, week 4, or week 10 after the first transfusion. A TTI will only be ascribed when both the donor unit and recipient have the exact same pathogen as confirmed by specialized laboratory testing.

In addition, the clinical effectiveness of Mirasol-treated WB products compared to standard WB products in recipients will be evaluated by the following:
Incidence and characteristics of acute transfusion reactions as defined by CDC Hemovigilance [31]Change in hemoglobin level post-transfusion compared to pre-transfusionDelayed transfusion reactions/neoantigenicity
i)Incidence of an amnestic RBC alloantibody as detected by a positive direct antiglobulin test (DAT) when participants are evaluated for transfusion reactionii)Incidence of new red cell alloantibodies post-transfusion (positive antibody screen at 10 weeks)Incidence of treatment-emergent adverse events (TEAE) and treatment-related adverse events

In order to assess the primary and secondary outcomes, the following laboratory tests will be performed (Fig. 1):

● Complete blood counts (CBCs)

● RBC antibody screen and direct antiglobulin test (DAT). The antibody screen will be used to determine new RBC alloantibody identification. If there is a suspected acute hemolytic transfusion reaction, a DAT will be performed. If the DAT is positive, antibody identification will be performed to determine whether it is a RBC alloantibody or a new antibody due to Mirasol PRT [32, 33].

● Bacteria: Cultures will be performed for both the donor unit and recipients. A TTI will only be ascribed when both the donor unit and recipient have the exact same genus and species.

● Viral TTIs: Serology assays for HIV (antigen and antibody combination), HBV (HBsAg, HBcAb), HCV (anti-HCV), HEV (IgG, IgM, and antigen), and HHV-8 (based on epitopes in open reading frames 73 and K8.1) will be performed on both donor units and recipients. The recipients will be evaluated at the last follow-up time point (week 10). If the recipient is positive, the other time points (i.e., enrollment (baseline), 48 h, day 7, and week 4) will subsequently be evaluated. HBV, HCV, HEV, and HIV nucleic acid testing (NAT) will also be performed among all donors and also for recipients at week 10, similar to serology testing.

● Malaria: Peripheral smears (thin and thick) will be performed among donor samples and on recipients at 48 h, day 7, and week 4. PCR assays will also be conducted to increase sensitivity [35]. The reading of the smears and PCR tests will be done retrospectively on stored samples and the results will not be available before transfusion. Two positive malaria PCR tests in the recipient post-transfusion samples are required to ascribe a malaria infection.

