#### *Plasmodium* allelic discrimination

If parasitemic blood is transfused to a non-parasitemic patient and parasitemia is identified post-transfusion, representative genes of the *Plasmodium* genome will be amplified for comparison between the donor and recipient to determine if the parasitemia was transfusion-transmitted or community-acquired. Donor and recipient samples will be compared when both are confirmed positive by initial testing (i.e., peripheral smear or nucleic acid). Allelic discrimination will be conducted using nested PCR of informative genome regions to further identify *Plasmodium* species. Sequencing of the representative genes will further discriminate between *Plasmodium* present in transfused WB products and in the patient post-transfusion [36]. Further high-resolution analyses based on genomic methods will also be considered [37]. Transfusion transmission will be assessed by matching up to three alleles present in donor and patient. The polymorphism of each allele is variable and will be considered in the interpretation of transfusion-transmitted malaria.

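### The two-PCR malaria rule does not say which samples count, so it cannot separate donor parasite DNA carried over early after transfusion from true transmission

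*Protocol article*

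**What the plan says.** The malaria item under Intervention outcomes sets the schedule: "Peripheral smears (thin and thick) will be performed among donor samples and on recipients at 48 h, day 7, and week 4". It adds that "PCR assays will also be conducted to increase sensitivity", and then gives the event rule: "Two positive malaria PCR tests in the recipient post-transfusion samples are required to ascribe a malaria infection". The rule does not name qualifying visits, a minimum spacing, a positive smear or a rising parasite density.

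The visit list under Assignment of intervention allows the 48 h draw one extra day and the day 7 draw one day early to two days late. The 48 h draw is tied to every transfusion, not only the first: "of each transfusion: blood collected for bacterial culture and malaria identification".

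The Introduction describes how Mirasol works: "The chemical reaction between riboflavin and UV light prevents DNA and RNA replication". It also says that the process breaks bonds in nucleic acids and irreversibly modifies some of their functional groups.

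On linkage, the Plasmodium allelic discrimination section says: "Transfusion transmission will be assessed by matching up to three alleles present in donor and patient". The stated purpose of typing is to tell parasites that came from the unit from those acquired in the community. The Analysis plan counts, in the primary analysis, recipients who turn positive after receiving a unit confirmed to contain the agent. The secondary analysis restricts to genetically linked events.

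**The concern.** The intervention is meant to stop parasites replicating. The article does not say that it removes their DNA from the unit. PCR detects DNA and does not show whether the parasite is alive. A recipient can in principle be PCR-positive shortly after transfusion because donor material is still circulating, whether or not an infection follows. In the Mirasol arm, such a case would be a success of the treatment scored as a failure.

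The other conditions for an event do not close this gap:

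- **Negative before transfusion.** This cannot exclude DNA that arrives with the unit.
- **Agent confirmed in the unit.** Every carry-over case meets this by definition.
- **Allele match.** Carried-over DNA is the donor's DNA, so it would be classed as linked.
- **Two positives.** This protects against one spurious or transient result, but not against DNA that lasts over two early draws, or that arrives with two different units.

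Bacteria are identified by culture, which needs viable organisms, so that component is not affected in the same way. Malaria is the largest expected component of the composite (13 of 31 control events under Study power calculations). What is at stake is whether the malaria, composite and linked results measure transmission or a mixture of transmission and carry-over.

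**Working it through.** **1. Can two early samples meet the rule?** The latest 48 h draw is day 2 + 1 = day 3. The day 7 draw runs from day 6 to day 9. Two qualifying positives can thus be 3 days apart (days 3 and 6), and both always fall within the first 9 days. About half of participants are expected to have at least two transfusions, each with its own 48 h draw, so two 48 h positives after different units also satisfy the wording.

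**2. The plan's own figures.** From Table 1, halving HEV and HHV-8 for prior immunity: 0.2 + 0.5 + 0.4 + 6.8/2 + 12.4/2 + 15.0 + 11.3 = 37.0 per 1000, which is the stated 3.7%. Power uses the two-proportion formula with continuity correction, 850 per arm, two-sided alpha 0.05, p2 = 0.2 × p1:

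n0 = [z(α/2)·√(2·p̄·q̄) + z(β)·√(p1·q1 + p2·q2)]² / (p1 − p2)²

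n = (n0/4)·[1 + √(1 + 4/(n0·|p1 − p2|))]²

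Solving for power at n = 850 gives 97.9% for any TTI (stated 97%) and 65.7% for malaria at 1.5% (stated 64%). Both reproduce within 2 points. Without the continuity correction, malaria power would be 74.6%, so the corrected formula is used below.

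**3. Adding carry-over.** Expected parasitemic units per arm: 850 × 1.5 × 5% = 63.75, treated as one per exposed recipient. True transmission is 20% in control and, at 80% efficacy, 4% with Mirasol. Let cC and cM be the share of exposed but uninfected recipients with two early positive PCRs in control and Mirasol. The document gives neither; both are assumptions.

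- Control malaria events: 63.75 × (0.20 + 0.80·cC) = 12.75 + 51.0·cC
- Mirasol malaria events: 63.75 × (0.04 + 0.96·cM) = 2.55 + 61.2·cM
- Other TTIs: control 31.45 − 12.75 = 18.70; Mirasol 0.2 × 18.70 = 3.74

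Equal carry-over, cC = cM = c:

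| c | Malaria events, control v Mirasol | Apparent malaria efficacy | Malaria power | Composite events, control v Mirasol | Apparent composite efficacy | Composite power |
|---|---|---|---|---|---|---|
| 0 | 12.75 v 2.55 | 80% | 66% | 31.45 v 6.29 | 80% | 98% |
| 5% | 15.30 v 5.61 | 63% | 48% | 34.00 v 9.35 | 72.5% | 95% |
| 10% | 17.85 v 8.67 | 51% | 36% | 36.55 v 12.41 | 66% | 92% |
| 20% | 22.95 v 14.79 | 36% | 22% | 41.65 v 18.53 | 55.5% | 83% |

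**4. Unequal carry-over.** If cM is half of cC, composite power stays near 97.5% for cC from 5% to 20%, while apparent composite efficacy falls to 77% (cC = 5%) and 70% (cC = 20%).

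**5. Where the direction turns.** Apparent malaria efficacy stays at 80% when 2.55 + 61.2·cM = 0.2 × (12.75 + 51.0·cC), that is 61.2·cM = 10.2·cC, or cM = cC/6. Below that, efficacy is overstated. With cC = 10% and cM = 0, malaria events are 17.85 v 2.55, an apparent efficacy of 86%.

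**The case against.** The strongest reply is that nothing in the document shows donor DNA persisting to both 48 h and day 6 to 9, so c may be close to zero and the two-positive rule may already do its work. This stands as a limit on size. It does not repair the rule, which would accept such cases if they occur and would leave no trace of how many there were.

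A reader might infer that the rule biases the trial against Mirasol. The document does not support that. The Introduction also describes damage to the nucleic acids themselves, and the article does not say whether PCR amplifies DNA damaged in this way. Equal carry-over in the two arms is only one scenario; dilution requires Mirasol-arm carry-over above one sixth of control's.

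A reader might also infer that efficacy at the 48 h visit suffers most. After a single transfusion the 48 h sample cannot make an event on its own, and the article does not say to which visit an event is dated.

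The primary comparison is fairly robust: with equal carry-over of 10%, composite power is still 92%, above the plan's 90% mark. Malaria alone was never a powered comparison. Both points stand. Power is not the main issue, however; the efficacy estimate would still change meaning.

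Finally, a condensed article may leave detail to the analysis plan, which is not shown. It may refine the rule. But the article itself states the event definition, and none of the sensitivity analyses that it lists addresses early-only positives.

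**Conclusion.** The point holds as a weakness of the endpoint definition. As written, malaria events can rest wholly on early samples, and no stated condition separates carried-over donor DNA from transmission in the primary or the genetically linked analysis. No planning figure is wrong: 3.7%, 97% and 64% all reproduce.

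Size and direction are not established. The efficacy losses in the table rest on an assumed carry-over of 5 to 20% that is equal in both arms; with little carry-over in the Mirasol arm the error runs the other way. What can be said is that the trial, as defined, would not be able to tell which of these happened.

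**What to change.** Keep the primary rule. Before unblinding, pre-specify a sensitivity analysis of the primary, malaria and genetically linked endpoints. In it, a malaria event that rests only on early samples (48 h and day 7, or repeated 48 h samples) does not count unless a positive day-7 smear or a positive week-4 sample supports it. For recipients of several transfusions, state from which transfusion the timing runs. Report by arm how many malaria events rest only on early PCR positives; that count shows how much the unknown carry-over could matter.

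The cost is a little more analysis. Smears and PCR are already planned at these visits and read retrospectively on stored samples, so no new visit, draw or assay is needed. Changing the primary definition itself is harder to justify. It would give up some of the sensitivity that PCR was added to provide, a rule based on rising DNA may need quantitative PCR, which the article does not mention, and more than 700 participants had already been recruited. The sensitivity analysis has its own weakness: it may miss some true smear-negative infections that are cleared or treated before week 4. It should therefore be read beside the primary result and not in place of it.
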